### Missing data and extreme values

Missing data are anticipated in some variables; notably BMI, blood pressure and smoking status. If comorbidities are missing they will be assumed to be absent. Missing values arise twice: first when calculating the QRISK2 score post hoc, and second when constructing the multivariable model. These citations will be accounted for differently.

Where data are missing from variables used in QRISK2 calculations, the imputed values used by the QRISK2 calculator will be used.^46^ In the multivariable model, all variables will be categorical and a ‘missing’ category will be used to account for the possibility that missing data are associated with the initiation of statins. Biologically implausible values for blood pressure, lipids, liver transaminases, height and weight will be identified and excluded.

## Analysis

Continuous variables will be categorised. Calculated and coded QRISK2 scores will be categorised according to risk bands (<10%, 10–14.9%, 15–19.9% and ≥20%). Age will be categorised into four groups (40–49, 50–59, 60–69 and ≥70). Total cholesterol (TC) will be categorised into three bands (<5.0, 5.0–6.9 and ≥7.0 mmol/L), and high-density lipoprotein (HDL) cholesterol into four bands (≤1.2, 1.3–1.4, 1.5–1.7 and ≥1.8 mmol/L) as these cut-offs have been used previously in the literature.^22^ Systolic blood pressure will be split into three groups corresponding to normotensive, stage 1 hypertension and stage 2 hypertension (<140, 140–159 and ≥160 mm Hg).^6^

The cohort will be described and prescribing rates and QRISK2 score trends will be established.

The primary analysis will consist of predictive modelling using multivariate logistic regression (variables summarised in table 1). Clustering of responses within individual general practitioner (GP) practices will be included in the model. Variation throughout the year due to the seasonality imposed by the Quality and Outcomes Framework (QOF) targets will be accounted for by adding the year quarter as a variable in the model. Assuming a minimum sample size for analysis of 10 per degree of freedom,^47^ and 57 degrees of freedom in the variables, a minimum sample of 570 patients with a lipid profile and subsequent statin initiation should easily be obtained.

**Table 1 BMJOPEN2016013120TB1:** Variables used in predictive modelling

Variable	Categories
Total cholesterol	<5.0, 5.0–6.9, ≥7.0
TC/HDL ratio	≤1.2, 1.3–1.4, 1.5–1.7, ≥1.8
Prior cholesterol measurements	0, 1–2, 3–4, ≥5
Calculated QRISK2	<10%, 10–14.9%, 15–19.9%, ≥20%
Coded QRISK2	<10%, 10–14.9%, 15–19.9%, ≥20%, missing
Systolic BP	<140, 140–159, ≥160, missing
Age	40–49, 50–59, 60–69, ≥70
Sex	Male, female
Ethnicity	White, Asian, black, other, missing
Townsend deprivation quintile	1st, 2nd, 3rd, 4th, 5th, missing
Urban/rural score	Urban, rural, missing
BMI	<20, 20–24.9, 25–29.9, 30–34.9, 35+, missing
Smoking status	Current smoker, ex-smoker, non-smoker, missing
Liver transaminases	Normal, abnormal, missing
Diabetes mellitus	Yes, no
Family history of CVD	Yes, no
Atrial fibrillation	Yes, no
Rheumatoid arthritis	Yes, no
Hypertension	Yes, no
Chronic kidney disease	Yes, no
HIV	Yes, no
Severe enduring mental illness*	Yes, no
Inflammatory conditions†	Yes, no
Antipsychotic medication	Yes, no
Long-term corticosteroids	Yes, no
Immunosuppressant medication	Yes, no
Year quartile	1st, 2nd, 3rd, 4th

*Schizophrenia, bipolar affective disorder, mania or psychosis (unspecified), psychotic depression.

†Systemic lupus erythematosus, scleroderma, Bechet's syndrome, other inflammatory arthritis.

BMI, body mass index; BP, blood pressure; CVD, cardiovascular disease; HDL, high-density lipoprotein.

The potential cohort size can be estimated from the literature. Feasibility data from the THIN database identified over 360 000 patients over 2 years who were eligible for statin treatment for the primary prevention of CVD and had a lipid result and blood pressure coded on their medical record.^22^ Over a 5-year period we should expect to identify over double this number. Another cohort identified just over two million patients in the THIN database in the age range where NHS health checks are offered.^48^ Given that every patient who attends an NHS health check should have a lipid test undertaken and 20% of 40–75 years old are invited to have a health check each year, with ∼50% taking up this offer.^49^ This would generate around 200 000 coded lipid results in the target population annually.

The accuracy of the post hoc QRISK2 calculations will be tested through comparisons with corresponding coded QRISK2 scores in patients where these are available.

Additional modelling will also be undertaken to consider whether having a QRISK2 score coded on the medical record affects the probability of having a statin prescribed after adjustment for the level of CVD risk. Secondary analysis will also establish whether the threshold for initiating statins has changed over the course of the study period. The mean lipid levels and QRISK2 scores (both coded and calculated post hoc) of those initiated on statins and those not initiated on statins will be calculated each year to reveal any trends in the thresholds for initiation.

Finally, prescriber-level data will be analysed to establish whether individuals tend to be influenced more by lipid levels or risk score when initiating stains and whether this behaviour is consistent over time. A score that illustrates the propensity to prescribe based on lipid levels will be calculated for individual clinicians. This will be generated by comparing the number of statin initiations to patients with a total cholesterol of ≥6.5 mmol/L with the number of statin initiations to patients with a total cholesterol of <6.5 mmol/L. Only clinicians who initiated 10 or more statin prescriptions over the study period will be analysed as scores for clinicians with fewer initiations may not be representative of their behaviour. The distribution of these scores will be described. For clinicians who initiated statins in every year of the study, their score will be calculated for the 2-year periods 2012–2013 and 2015–2016. The scores for each period will be split into quintiles. The tendency for clinicians to stay in the same quintile, or move quintile, will then be described.

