## Study variables

### Exposure variables

The exposure of interest is the undertaking of lipid testing. Once a patient has their lipids recorded, this signifies that a clinician has made a decision about the significance of the lipid levels and will act on this. Individual patients may have multiple lipid results recorded over the study period. Assuming the exclusion criteria are not met, each lipid result will be considered as a new exposure so long as it is not within 60 days of the last recorded lipid level. The number of previous lipid results will be included in predictive modelling.

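### The objective 3 estimate of what a coded QRISK2 score does to statin prescribing may be confounded by the reason for testing, because no listed variable separates NHS Health Check tests from other lipid tests

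*Protocol article*

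**What the plan says.** All references are to the protocol article.

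- **Exposure variables:** "The exposure of interest is the undertaking of lipid testing". Each eligible result more than 60 days from the last counts as a new exposure, whatever led to the test.
- **Analysis (cohort size):** one of two feasibility estimates rests on NHS Health Checks: "Another cohort identified just over two million patients in the THIN database in the age range where NHS health checks are offered", "every patient who attends an NHS health check should have a lipid test undertaken", "20% of 40–75 years old are invited to have a health check each year, with ∼50% taking up this offer", and "This would generate around 200 000 coded lipid results in the target population annually". The other is a count of eligible patients: "Feasibility data from the THIN database identified over 360 000 patients over 2 years", limited to those with both a lipid result and a blood pressure on record.
- **Analysis (additional modelling):** the model for objective 3 asks whether having a QRISK2 score on the record "affects the probability of having a statin prescribed after adjustment for the level of CVD risk". No other covariate is named for it.
- **Predictor variables and Table 1:** neither lists Health Check attendance or the reason for the test.
- **Potential limitations:** this section covers scores calculated or displayed but not coded, and tests or prescriptions originating outside primary care. It does not mention Health Checks.

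**The concern.** Objective 3 is worded as the contribution of calculating a score, and the matching analysis asks whether a coded score affects prescribing. Both wordings are causal. The comparison is between tests with and without a coded score, and those two groups may differ in how the test came about. Some patients are tested because a programme invited them, others for other reasons.

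If the programme makes it more (or less) likely that a score is coded, and its attenders start statins at a different rate from other patients with the same risk, the coded-score odds ratio mixes a pathway difference with any effect of the score. Adjusting for the level of CVD risk, or for every variable in Table 1, does not identify the pathway. The expected cohort is very large, so a biased odds ratio would come with a narrow confidence interval and could be read as firm evidence about risk scoring.

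**Working it through.** **1. The plan's own figure.** Patients in the Health Check age range, about 2 000 000; 20% invited each year; about 50% attend; one lipid test each:

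2 000 000 × 0.20 × 0.50 = 200 000 a year.

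This reproduces the stated figure. The sentence on cohort size is arithmetically correct.

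**2. Can a share of exposures be derived?** The other estimate gives 360 000 / 2 = 180 000 patients a year. Read as part over whole, 200 000 / 180 000 = 1.11, or 111%, which is impossible. The two figures do not share a denominator. The 2 000 000 are described only by age range, not as free of CVD and statins. The 360 000 are eligible patients, not results, and needed a coded blood pressure. So Health Check tests are expected to be numerous, but no share follows.

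**3. Does any listed variable mark the pathway?** The Predictor variables section and Table 1 cover sociodemographic details, QRISK2 components, other clinical conditions, medication, number of earlier cholesterol measurements and quarter of the year. None marks a Health Check test.

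**4. How large could the bias be?** None of the inputs below is in the documents. Let *s* be the share of tests from Health Checks, *c₁* and *c₀* the probability of a coded score at Health Check and other tests, and *p₁* and *p₀* the initiation probability at equal risk. Coding has no true effect (odds ratio 1.0).

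- Coded: [s·c₁·p₁ + (1−s)·c₀·p₀] / [s·c₁ + (1−s)·c₀]
- Uncoded: [s(1−c₁)p₁ + (1−s)(1−c₀)p₀] / [s(1−c₁) + (1−s)(1−c₀)]

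Example: s = 0.5, c₁ = 0.6, c₀ = 0.1, p₁ = 4%, p₀ = 7%.

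- Coded: (0.5×0.6×0.04 + 0.5×0.1×0.07) / 0.35 = 0.0155 / 0.35 = 4.43%
- Uncoded: (0.5×0.4×0.04 + 0.5×0.9×0.07) / 0.65 = 0.0395 / 0.65 = 6.08%
- Spurious odds ratio: (0.0443/0.9557) / (0.0608/0.9392) = 0.72

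Range over s = 30–70%, c₁ = 40–80%, c₀ = 10–15%:

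| Initiation, Health Check v other | Spurious odds ratio |
|---|---|
| 4% v 7% | 0.66 to 0.85 |
| 5% v 6% | 0.87 to 0.95 |
| 7% v 5% | 1.08 to 1.29 |

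A second set of assumptions uses 5% initiation at other tests, a Health Check share of 20% or 50%, and a prescribing odds ratio for Health Check v other tests between 0.5 and 2.0. It gives 0.80 to 1.24 with coding 50% v 20%, and 0.61 to 1.60 with coding 80% v 10%.

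**5. When is there no bias?** With equal coding in both pathways (30% v 30%), the spurious odds ratio is 1.00 whatever the initiation rates. With equal initiation at equal risk, it is 1.00 whatever the coding rates. Both links are needed.

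**The case against.** The strongest reply is that the documents establish neither link. They do not say that scores are coded more often at Health Checks, or that attenders are prescribed statins differently at the same risk. The illustration can be pushed either side of 1 by choice of inputs, its worked example uses the widest of the three initiation contrasts, and the mild contrast moves the odds ratio only to between 0.87 and 0.95. All of this stands. It rules out saying that the estimate will be biased, or in which direction.

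The article also describes the additional modelling in a single sentence, and the code lists are in an appendix that is not shown. The codes may therefore already be held. This lowers confidence somewhat, but Table 1 sets out the variables for predictive modelling and has no such indicator.

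A further reply is that attendance may be how a score comes to be calculated, so that adjusting for it changes the question. But attendance then comes before the coding of the score and does not follow from it. For an effect of the score itself, it is a candidate confounder. Reporting the estimate with and without the indicator shows the reader both quantities.

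Three stronger readings are tempting and are not supported:

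- **That Health Checks could supply most exposures.** Setting 200 000 beside 180 000 a year invites this, but the figures are not part and whole.
- **That the Exposure variables section is contradicted by programme testing.** It says of a recorded result that "this signifies that a clinician has made a decision about the significance of the lipid levels and will act on this". That concerns how a result is handled once on the record, not who prompted the test. An invited patient's result also has to be interpreted.
- **That the objective 1 answer is biased.** The introduction sets out to describe decisions in routine practice, and the primary analysis is predictive. An average over the ways tests arise in practice fits that target.

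**Conclusion.** The point holds as a possible confounder of objective 3, and of that objective only. It rests on three things the article does state: all lipid results are pooled, Health Checks are expected to generate many of them, and no listed variable tells them apart while the result is worded as an effect of the score. Whether bias occurs depends on two links that the documents do not give.

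If both exist, the assumed ranges put the spurious odds ratio roughly between 0.6 and 1.6, with no known direction. If either is absent, there is none. The size is illustrative, but the gap can be closed cheaply and is worth closing before the objective 3 result is interpreted.

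**What to change.** Where attendance codes are available, extract a Health Check indicator (yes/no) for each lipid result and add it to the objective 3 model. Report the coded-score odds ratio without the indicator, with it, and separately for Health Check and other tests. If the codes prove too incomplete, add the reason for testing to the limitations and word the objective 3 result as an association, not as an effect or contribution of the score.

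The cost is one more code list, one stratified table and one degree of freedom. Under the plan's rule of 10 initiations per degree of freedom, that is ten more (570 to 580 if set against the stated 57 degrees of freedom). The downside is that uncoded Health Checks would be classed as other tests, leaving some residual mixing. If recording of the check and of the score tend to go together, that misclassification would bear directly on the comparison of interest, so the completeness of the codes should be described alongside the result.

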^29^ It may appear logical that decisions about initiating cholesterol-lowering medication should be based on the patient's cholesterol level, and indeed this was the preferred approach in the pre-CVD risk era.^30^
^31^ However, this approach would not necessarily result in the greatest benefits and is not justifiable based on the available evidence. Despite this, there is evidence that this approach prevails in some areas. After adjusting for other CVD risk factors, lipid profile has been found to predict statin initiation in a US study^32^ and a randomised theoretical experiment in Australia highlighted clinicians’ preferences for managing individual risk factors over absolute risk.^33^ To further compound the problem, patients find it difficult to make decisions based on future risks and tend to preferentially focus on cholesterol levels when considering taking statins.^34^
^35^

In 2014, guidelines for England and Wales on lipid modification reduced the predicted risk threshold at which patients should be offered statins from a 20% 10-year risk to 10%.^5^
^7^ This recommendation was met with considerable concern from the medical community that it would lead to widespread overprescribing of statins with little clinical benefit but considerable potential for harm.^36^
^37^ This widely publicised criticism may have increased concerns that risk scoring leads to oversimplification of clinical decisions and overprescribing and may have, perversely, decreased the use of risk scoring and reinforced the use of lipid levels to guide decision-making. There is some evidence to suggest there was a decrease in statin initiations around this time due to the negative media attention.^38^

This research will investigate the relationship between lipid profile, QRISK2 score and subsequent initiation of statins by primary care clinicians. This will give an indication of the patient factors that are influencing the decisions clinicians make in routine practice when considering the use of statins and how this has changed in response to external factors.

The consistent use of risk scoring can result in more targeted prescribing and fewer patients being prescribed medication overall^39^ which maximises the efficiency and cost-effectiveness of treatment at a population level.

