## Aims and objectives

*Aim*: To establish whether UK primary care patients are initiated on statins based more on their lipid levels or on their predicted CVD risk and if this has changed over time.

*Objectives*:

For primary prevention of CVD
To evaluate how lipid levels and CVD risk independently predict subsequent prescribing of statins.To determine if the relationship between lipid levels, QRISK2 score and statin prescribing has changed following recent guideline changes.To investigate the contribution that calculating a QRISK2 score has on the probability of initiating statin therapy.To investigate interprescriber variation when initiating statins.

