### Population

Patients will be eligible for inclusion if they are aged between 40 and 84 years inclusive (the age range recommended by the National Institute for Health and Care Excellence (NICE) for risk assessment^5^) with no previous diagnosis of CVD and at least one lipid result coded in the study period. The date of the first coded lipid result in the study period will be considered the index date. Patients must not have been prescribed a statin prior to the index date.

In order to maintain a stable cohort of practices, only THIN practices in which there are data available for the whole study period will be included. The study period will run from the beginning of 2012 to the end of 2016. Patients will be eligible for inclusion from the earliest of the following dates: study start date, acceptable mortality reporting date (which ensures that patient deaths and deregistrations are being recorded consistently^45^), Vision date plus 1 year, registration date plus 1 year (to ensure time for baseline data to be recorded), and age 40; until the earliest of the following dates: age 85, study end date, CVD diagnosis, other excluding diagnosis (as below), statin initiation or recording of a contraindication for the prescribing of statins. Patients will also be excluded if they left the database within 60 days of the index date.

Patients will be excluded if they had pre-existing CVD, were pregnant, had a contraindication to statin therapy (including allergies and drug interactions), were already being prescribed a statin (or other lipid-lowering therapy) or had ever been prescribed a statin in the past. Patients will be considered to have pre-existing CVD if they had a diagnosis of myocardial infarction, angina, peripheral vascular disease or stroke/transient ischaemic attack. Patients with type 1 diabetes mellitus, a diagnosis of chronic kidney disease stages 3–5 and patients diagnosed with or who were at risk of familial hypercholesterolaemia will also be excluded as statin use in these patients should not be based on CVD risk assessment. Patients at risk of familial hypercholesterolaemia will be defined as those with a total cholesterol of ≥9.0 mmol/L as this is the threshold for seeking specialist assessment defined in the NICE guidance.^5^

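### Objective 2 asks whether prescribing changed after the 2014 guideline, but its only named analysis is unadjusted yearly group means, which changes in who is tested can mimic or mask

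*Protocol article*

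**What the plan says.** All references are to the protocol article.

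- **Aims and objectives.** The aim is to learn whether initiation is "based more on their lipid levels or on their predicted CVD risk and if this has changed over time". Objective 2 is "To determine if the relationship between lipid levels, QRISK2 score and statin prescribing has changed following recent guideline changes".
- **Introduction.** The guideline change in question is that of 2014, which "reduced the predicted risk threshold at which patients should be offered statins from a 20% 10-year risk to 10" per cent.
- **Population.** "The study period will run from the beginning of 2012 to the end of 2016", so the data span the change.
- **Analysis, secondary analysis.** The stated purpose is: "Secondary analysis will also establish whether the threshold for initiating statins has changed over the course of the study period". The method for change over time is that mean lipids and mean QRISK2 (coded and calculated) "of those initiated on statins and those not initiated on statins will be calculated each year to reveal any trends in the thresholds for initiation".
- **Analysis, primary model and Table 1.** Time enters only "by adding the year quarter as a variable in the model", to allow for seasonality from Quality and Outcomes Framework targets. Table 1 lists no calendar year, no period before or after the guideline, and no interaction.

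**The concern.** Objective 2 is a question of effect modification: did the dependence of prescribing on QRISK2 and on lipids differ before and after the guideline? The article answers it with two series of unadjusted means and calls their movement a trend in thresholds. A mean among initiated patients is not a threshold. It combines the prescribing rule with the risk distribution of those tested, and in an open cohort that distribution can move from year to year. No adjustment, contrast or test is named to separate the two.

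At stake is the second half of the aim. A drift in who is tested could be reported as a response to the guideline, or a real response could go unseen.

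**Working it through.** **1. The plan's own figure.** The Analysis section takes 10 initiations per degree of freedom and 57 df: 10 × 57 = 570, as stated. Counting Table 1 as categories minus one over its 27 variables gives 58 df, hence 580. The difference is immaterial.

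**2. Time terms in the model.** Year quarter has four categories (3 df) and repeats every year. A result from the first quarter of 2012 and one from the first quarter of 2016 have the same value. No parameter can differ before and after 2014.

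**3. Why a mean is not a threshold.** For year y, let f_y(q) be the QRISK2 distribution of those tested and p_y(q) the probability of initiation at risk q.

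- Mean of the initiated = ∫ q·p_y(q)·f_y(q) dq ÷ ∫ p_y(q)·f_y(q) dq.
- Mean of the not initiated: the same with 1 − p_y(q).

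Objective 2 is about p_y. Both means also contain f_y, so either can move while p_y stays fixed.

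**4. Illustration.** Every input here is an assumption; none comes from the documents.

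- 100 000 lipid results a year for five years.
- QRISK2 log-normal, median 11%, log-SD 0.8, capped at 80%. Total cholesterol normal, mean 5.5, SD 1, independent of QRISK2.
- Logistic rule with intercept −4.5. Log-odds 0, 1.0, 1.6, 2.2 over the plan's four QRISK2 bands and 0, 0.8, 2.0 over its three cholesterol bands. About 7% are initiated.
- Real change: from 2015 the QRISK2 log-odds become 0, 2.0, 2.3, 2.5.
- Drift: median QRISK2 of those tested moves by 5% of its starting value per year.
- Comparison model: logistic, with a 2015–2016 term and its interactions with the QRISK2 and cholesterol bands.

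| Rule / drift | Initiated mean, 2012→2016 | Not initiated mean | Gap | Crude initiation rate | Period × QRISK2 |
|---|---|---|---|---|---|
| Fixed / none | 23.64→23.76 | 14.20→14.26 | 9.44→9.50 | 7.35→7.47% | p = 0.67 |
| Fixed / −5% | 23.47→20.20 | 14.25→11.48 | 9.22→8.71 | 7.47→6.14% | p = 0.82 |
| Fixed / +5% | 23.85→26.53 | 14.29→17.04 | 9.55→9.49 | 7.33→8.55% | p = 0.42 |
| Changed / none | 23.36→22.10 | 14.31→14.01 | 9.05→8.09 | 7.39→11.00% | 1.02 (SE 0.04) in the 10–14.9% band; true value 1.0 |
| Changed / +5% | 23.58→24.92 | 14.24→16.83 | 9.34→8.09 | 7.50→12.71% | 0.99 (SE 0.04) in the same band |

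Drift alone lowered the initiated mean by 23.47 − 20.20 = 3.27 points; the real change alone lowered it by 23.36 − 22.10 = 1.26. With upward drift, the real change appeared as a rise of 24.92 − 23.58 = 1.34. The interaction stayed null where nothing had changed and recovered the change where it had.

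These are single runs. The fitted model used the same bands as the simulated rule, and clustering and repeat results were left out. They show that means can mislead in either direction, not how far they would in this database.

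**5. Size of the remedy.** Calendar year 4 df + period × calculated QRISK2 3 df + period × total cholesterol 2 df = 9 df. 57 + 9 = 66 df, or 660 initiations at 10 per df (67 and 670 from the count of 58). If the period boundary falls inside 2014, period needs its own main effect, 1 df more. Full year interactions would add 4 + 12 + 8 = 24 df: 81 df, 810 initiations. The article expects around 200 000 lipid results a year, so about 1 000 000 over five years; 660 ÷ 1 000 000 = 0.066%.

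**The case against.** **The not-initiated means are reported too.** This is the best defence. A parallel shift in both groups points to drift, and in the simulation the gap between groups was steadier under drift (9.22→8.71 and 9.55→9.49) than under real change (9.05→8.09 and 9.34→8.09). That stands as a useful hint. But the plan does not name the gap as its contrast, gives no test, and has no way to turn a narrower gap into a statement about a threshold. With nothing changing at all, the simulated yearly gap still ranged from 8.96 to 9.54.

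**Other time analyses are planned.** The Analysis section also promises prescribing rates and QRISK2 trends, and these would give context: a jump in the crude rate from 7.50% to 12.71% would be noticed. Crude rates also move with case mix, however, and do not show where on the risk or cholesterol scale prescribing changed. The prescriber analysis compares 2012–2013 with 2015–2016, but its score uses cholesterol alone, and quintiles formed within each period cannot show an overall shift.

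**A fuller analysis plan may exist.** It may, but the article does more than stay silent: it names the method for this question and claims that the method will establish the answer.

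**Stronger readings a reader might infer.** One is that drift will certainly mislead. The documents give neither its size nor its direction, and keeping a stable set of practices limits one source of it. Another is that removal of patients at initiation must push the means a known way. That does not follow, because the Population section also provides entry at age 40 and after registration, and exit at age 85 and at CVD diagnosis; the net direction depends on their balance. A third is that pooling 2012–2016 invalidates the primary odds ratios. Objective 1 makes no claim about time, and a period average is a legitimate target for it.

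**Conclusion.** The point holds, limited to objective 2 and the matching half of the aim; it should be fixed. The named method cannot separate a changed prescribing rule from a changed mix of tested patients, and no model term does so either. This follows from the form of the means and from Table 1 and needs no assumed drift; only the illustrative magnitudes do. The primary analysis of objective 1 is unaffected.

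**What to change.** - For objective 2, fit the clustered logistic model with calendar year added, plus interactions of a pre/post-guideline period with calculated QRISK2 and with total cholesterol. Name these interactions as the analysis of objective 2. The authors must fix the boundary date, as the article gives only the year 2014.
- Report, for each year, the probability of initiation by QRISK2 band and by total cholesterol band among tested patients, standardised to a fixed case mix.
- Keep the yearly means as description, and stop calling them thresholds.

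The cost is the roughly 9 df derived above, a change to the text, and no new data. Ten initiations per df is a minimum for fitting the model, not a power calculation for the interactions, so report these with confidence intervals.

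### The clinician score compares counts of initiations above and below TC 6.5 mmol/L with no tested-patient denominator and no QRISK2, so it mixes behaviour with case mix; its event floor does not protect the quintile comparison

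*Protocol article*

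**What the plan says.** The last paragraph of the Analysis section introduces the prescriber-level work as a way "to establish whether individuals tend to be influenced more by lipid levels or risk score when initiating stains", and whether this holds over time. It serves the fourth objective, on interprescriber variation.

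The tool is described this way: "A score that illustrates the propensity to prescribe based on lipid levels will be calculated for individual clinicians". It is formed by "comparing the number of statin initiations to patients with a total cholesterol of ≥6.5 mmol/L with the number of statin initiations" on the other side of the cut, that is, "the number of statin initiations to patients with a total cholesterol of <6.5 mmol/L". No other quantity enters.

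Eligibility is set by a count: "Only clinicians who initiated 10 or more statin prescriptions over the study period will be analysed". The reason given is that scores from fewer initiations may not reflect how the clinician behaves.

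For stability over time: "For clinicians who initiated statins in every year of the study, their score will be calculated for the 2-year periods 2012–2013 and 2015–2016". Each period's scores are cut into quintiles, and "The tendency for clinicians to stay in the same quintile, or move quintile, will then be described".

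Elsewhere, the article makes every eligible lipid result an exposure whether or not a statin follows (Exposure variables). It also calculates a post hoc QRISK2 for all patients and records clinician ID (Predictor variables).

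**The concern.** There are two separate problems.

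- **What the score measures.** It describes only patients who were started on a statin. The split of those patients around 6.5 depends on how the clinician responds to cholesterol and also on how many of the clinician's tested patients had high cholesterol to begin with. With QRISK2 absent, no value of the score can set lipids against risk. Lipids are themselves a QRISK2 input, so a high share of initiations at high TC does not by itself indicate lipid-led rather than risk-led prescribing.
- **How precisely it is measured.** The article accepts that small counts mislead and sets a floor of 10 for that reason. The floor applies to the five-year total, but the quintiles are formed in two-year windows, where counts are smaller.

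At stake is the reading of objective 4. Differences between prescribers could be differences between their patients. Movement between quintiles could be chance, and staying put could be stable case mix. The Potential limitations section mentions neither case mix nor chance for this score.

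**Working it through.** **The plan's own figures.** The only sample-size calculation is for the primary model: 10 × 57 = 570 initiations, which reproduces. No precision figure is given for the clinician score, so everything below follows from its definition plus stated assumptions.

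**1. What the count ratio contains.** Let s be the share of a clinician's tested patients with TC ≥6.5, and RR the initiation rate at or above 6.5 divided by the rate below.

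Count ratio = s·RR / (1 − s). As a share of initiations: s·RR / (s·RR + 1 − s).

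- Same behaviour, different patients (RR = 1): s = 0.10 gives 0.10/0.90 = 0.11; s = 0.30 gives 0.30/0.70 = 0.43.
- Same behaviour, RR = 2 for both: 0.20/0.90 = 0.22 and 0.60/0.70 = 0.86.
- Different behaviour, same score: s = 0.10 with RR = 3.86 gives 0.386/0.90 = 0.43; s = 0.30 with RR = 1 also gives 0.43.

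The values of s are illustrative. The size of the distortion depends on how far clinicians' patients differ. With tested TC taken as normal with SD 1.0 (assumed) and RR = 1, clinician means of 5.2, 5.5 and 5.8 mmol/L give ratios of 0.11, 0.19 and 0.32, about threefold from end to end. Means of 5.4 and 5.6 give 0.16 and 0.23, about 1.4-fold. The documents do not say which is nearer the truth. More initiations per clinician do not remove this problem.

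**2. Events per window.** Ten initiations over five years average 10 × 2/5 = 4 per two-year window. The stability analysis needs one initiation in each year, so the minimum is 2 per window. With 1 of 4 initiations at high TC, the exact 95% interval for the share is 0.6% to 81%. At n = 4 the score can take only five values, so quintile cuts fall on ties.

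How typical the floor is cannot be read from the documents. As a rough range, over 360 000 patients in 2 years across over 500 practices is about 720 per practice. Assuming that 5% to 20% are initiated and that there are 10 to 4 clinicians per practice, this gives 720 × 0.05/10 = 3.6 up to 720 × 0.20/4 = 36 initiations per clinician per window.

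**3. Quintile stability when nobody changes.** Clinicians were simulated with a fixed true high-TC share (mean 0.35, assumed) and two independent windows of n initiations. Quintiles were cut in each window with ties broken at random. Reliability = SD² / (SD² + E[p(1−p)]/n), with E[p(1−p)] = 0.35 × 0.65 − SD².

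| True-share SD (assumed) | Same quintile, n = 4 | Same quintile, n = 20 | Same quintile, n = 36 |
|---|---|---|---|
| 0.05 | 21% | 24% | 26% |
| 0.10 | 23% | 32% | 37% |
| 0.15 | 26% | 39% | 47% |
| 0.20 | 31% | 48% | 56% |

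Repeat runs agree to within about one percentage point. Chance alone gives 20%. Reliability at n = 4 runs from 0.0025/(0.0025 + 0.225/4) = 0.04 to 0.04/(0.04 + 0.1875/4) = 0.46. At n = 36 it runs from 0.29 to 0.88.

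**4. The opposite error.** Give every clinician the same RR and let only s vary, stably (mean 0.20, logit SD 0.5, assumed), with n = 40. Then 36% (RR = 1) to 39% (RR = 2) stay in the same quintile. That would look like consistent individual behaviour although no two clinicians behave differently.

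**The case against.** The strongest reply has four parts.

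- **Behaviour is in the score.** RR appears in the formula and the score rises with it. A reader might infer that the score measures only case mix and chance. The definition does not support that: behaviour is present but cannot be separated from case mix. This part stands.
- **Small counts are not shown to be typical.** A reader might infer that the whole stability analysis rests on a handful of events. The documents give no distribution of initiations per clinician, and the rough range reaches 36 per window, where reliability may be good. The criticism is of what the floor permits. This part stands.
- **No verdict of inconsistency is planned.** Quintile movement is to be described, not tested. A reader might infer that the analysis would wrongly declare prescribers inconsistent, but step 4 shows that the error can run the other way, so its direction is not established. Nor can one say that the score is undefined when no initiation falls below 6.5: the article speaks of comparing two counts, and a proportion fits that wording.
- **Limited scope.** The main question of lipids against risk goes to the primary model, which uses all exposures, TC and calculated QRISK2. This is right, and it limits the importance of the point.

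None of this answers the core. The paragraph states a lipids-versus-risk question for individual clinicians and fixes a score that has neither a denominator nor a risk term. Since the construction is spelled out, the point concerns what is specified, not detail that an article might leave to a fuller plan.

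**Conclusion.** The concern holds in this form. The clinician score confounds behaviour with case mix and, lacking QRISK2, cannot show whether a clinician is influenced more by lipids or by risk. This follows from the definition and needs no assumption; only the size of the distortion does.

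The floor of 10 is applied to the wrong interval for the stability analysis. At the floor, quintile agreement among perfectly stable clinicians is close to chance or only moderately above it. At the top of the rough volume range it runs from barely above chance to 56%. These figures depend on the assumed mean share of 0.35 and SDs of 0.05 to 0.20, none of which the documents supply. Quintile movement can thus look inconsistent through chance or consistent through stable case mix.

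The effect is confined to objective 4, a descriptive secondary analysis. The primary model is untouched.

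**What to change.** - Base the prescriber analysis on all eligible lipid exposures. Either compare initiation rates (initiated/tested) at TC ≥6.5 and <6.5, adjusted for calculated QRISK2, or fit a mixed logistic model with clinician-level slopes for TC and QRISK2. The model is the fuller answer, because it estimates both influences for each clinician and shrinks imprecise estimates. In the example above, denominators would separate rate ratios of 3.86 and 1.
- Apply the minimum initiation count to each two-year window. Denominators alone do not reduce sampling noise.
- Report the between-period correlation allowing for sampling error, instead of or alongside raw quintile movement.

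**Cost.** Lipid exposures, calculated QRISK2 and clinician ID are already part of the planned data, so the cost is mainly analysis time. The real difficulty is that untreated tests must be attributed to a clinician, and the article does not say that the record always allows this. Where it does not, adjust for the TC and QRISK2 mix of tested patients at practice level and state the limitation; this only partly recovers the prescriber-level contrast. Fewer clinicians will qualify for the stability analysis.
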